### Study population and eligibility

2.5

*Inclusion criteria:* All women residing in the four study blocks who experience a stillbirth (intrauterine foetal death at ≥28 completed weeks of gestation) during the study period, are able to provide informed consent, and are reachable for an ASHA home visit.

*Exclusion criteria:* Women with severe cognitive impairment precluding informed consent, or those who explicitly decline participation.

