#### Primary effectiveness outcome

2.8.1

The primary effectiveness outcome will be the mean Edinburgh Postnatal Depression Scale (EPDS) total score (continuous, range: 0–30) at Day 60 postpartum (±2 days), measured by an independent study nurse (15). The EPDS was selected as the primary outcome on the basis that the primary target of C-COMPASS is the prevention of pathological depressive disorder following stillbirth, rather than grief resolution *per se*, a longer-term outcome beyond the scope of this first evaluation. The potential overlap between grief and depressive symptoms in the early postpartum period is acknowledged; this is addressed within the study design by the concurrent administration of the Brief Grief Questionnaire (BGQ) as a secondary outcome, enabling exploratory analysis of the relationship between grief and depression constructs in this population. The EPDS has been used in perinatal loss populations and validated in Indian perinatal settings (16, 17), and its use as the primary outcome enables direct comparison with the closest available LMIC analogue and alignment with NHM mental health referral thresholds.

Outcome assessment will be scheduled at Day 60, after the ASHA's Day 42 visit, to ensure a minimum three-day separation between the final C-COMPASS contact and outcome measurement, thereby minimising response priming and maintaining assessor independence. The EPDS captures symptoms over the preceding seven days; thus, administration at Day 60 reflects the post-intervention steady state. This timing is consistent with the original validation of the EPDS at 6–8 weeks postpartum (15).

Where Verbal Autopsy (VASA) is conducted for the same participant, EPDS, SDS, and BGQ will be administered first, preferably on a different day. If same-day administration is unavoidable, outcome measures will be completed prior to VASA to minimise recall-induced emotional bias.

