### Statistical analysis

2.13

The primary Difference-in-Differences (DiD) model will be specified as a linear regression with block fixed effects:$$EPDS=\beta_{0}+\beta_{1}(Arm)+\beta_{2}(Time)+\beta_{3}(Arm\times Time)+\gamma_{k}(Block_{k})+\epsilon$$where *Arm* (1 = intervention, 0 = control), *Time* (1 = post, 0 = pre), and the interaction term (*Arm* × *Time*) represents the DiD estimator (*β*₃). A negative *β*₃ will indicate a reduction in depressive symptoms attributable to C-COMPASS. Block fixed effects (*γ*_k_) will account for time-invariant block-level confounders, including baseline ASHA performance, population characteristics, and facility access.

The pre-specified secondary binary outcome (EPDS ≥ 13) will be analysed using a logistic DiD model with the same structure. SDS and BGQ scores will be analysed using linear DiD models with block fixed effects, while BGQ screen-positive (≥4) will be analysed using logistic DiD models. Implementation outcomes (visit completion, referral completion, and documentation completeness) will be reported as proportions with 95% confidence intervals.

Parallel trends will be assessed by comparing pre-intervention EPDS distributions across study arms and blocks, along with baseline sociodemographic characteristics (20). A maximum of one additional covariate beyond block fixed effects will be included, selected *a priori* (most likely gravida or previous stillbirth) (21). A pre-specified sensitivity analysis will replicate the primary model in an expanded population including early neonatal deaths, incorporating a perinatal loss type indicator and its interaction with the intervention effect. All analyses will be conducted using Stata version 16 or R version 4.4+.

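### The linear difference-in-differences model may adjust for at most one covariate, so a measured case-mix change that differs by arm can be corrected on only one variable, although the sample easily carries both candidates the plan names

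*Protocol article*

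**What the plan says.** Section 2.13 (Statistical analysis) of the protocol article specifies a linear regression of EPDS on Arm, Time, Arm × Time and block. The interaction coefficient β3 "represents the DiD estimator". On adjustment it states: "A maximum of one additional covariate beyond block fixed effects will be included". The variable is to be selected a priori and is "most likely gravida or previous stillbirth". Apart from a citation, no reason is given for the limit.

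The same section says that the block fixed effects "will account for time-invariant block-level confounders, including baseline ASHA performance, population characteristics, and facility access". Parallel trends are to be judged from pre-intervention EPDS distributions across arms and blocks, "along with baseline sociodemographic characteristics". These characteristics are not listed.

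Two other sections determine who is compared. Section 2.5 enrols women "who experience a stillbirth (intrauterine foetal death at ≥28 completed weeks of gestation) during the study period" who "are reachable for an ASHA home visit". Section 2.8.1 takes the primary outcome "at Day 60 postpartum (±2 days), measured by an independent study nurse".

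**The concern.** A woman enters because of a loss in a given period and gives one EPDS score, so the design is a repeated cross-section. β3 compares four groups of different women, and no baseline EPDS absorbs differences between individuals. Blocks are chosen purposively (Section 2.7), so randomisation gives no protection either.

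The model already removes two sources of difference. Stable differences between blocks go into the block effects, and changes shared by both arms, such as the July–October peak, go into Time. What remains is a pre-to-post change in the mix of women that differs between arms.

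The article contains a plausible route to such a change. Eligibility depends on being reachable for an ASHA visit, and from May 2026 only the intervention-block ASHAs are trained (Sections 2.6.4 and 2.7). If training changes which women are found and reached, the post-period intervention sample can shift in parity or obstetric history while the control sample does not. The cap allows adjustment for only one such characteristic. The comparison of baseline characteristics belongs to the pre-intervention parallel-trends check, so it does not address this change.

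**Working it through.** **Inputs from the article (Section 2.12).** Target difference 3.5 points; SD 6.5; two-sided alpha 0.05; about 17 women per arm before and 56 after; total 146. For EPDS ≥13: baseline 40% and a 16-point reduction, so 24%.

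**Inputs assumed, because the article gives none.** Arm-differential shift in prevalence 10–20 points; prognostic effect 2–4 EPDS points; for precision, a factor with 15% prevalence worth 3 points; covariate R² 0.05–0.30.

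**1. The plan's own figures.** A two-sample comparison with difference 3.5 and SD 6.5 needs 55 per arm, and 56 per arm gives 81% power by the normal approximation. Total: 2 × (17 + 56) = 146. All three reproduce. The power figure describes a post-period comparison and uses neither the interaction nor a covariate.

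**2. The contrast actually analysed.** With independent women, SE(β3) = SD × √(2/n_pre + 2/n_post) = 6.5 × √(2/17 + 2/56) = 2.55. Power for 3.5 points is Φ(3.5/2.545 − 1.96) = 28%. With 25 pre-period women per arm, which corresponds to the 12 weeks in Section 2.4, SE is 2.21 and power 35%.

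**3. Bias from a differential shift.** Bias in β3 = (difference-in-differences in prevalence) × (effect of the factor on EPDS), less whatever the one permitted covariate already explains.

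| Shift | 2 points | 3 points | 4 points |
|---|---|---|---|
| 10 percentage points | 0.20 | 0.30 | 0.40 |
| 15 percentage points | 0.30 | 0.45 | 0.60 |
| 20 percentage points | 0.40 | 0.60 | 0.80 |

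Against 3.5 points the range is 0.2/3.5 = 6% to 0.8/3.5 = 23%.

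**4. Precision from a second covariate.** A factor at 15% prevalence worth 3 points explains 3² × 0.15 × 0.85 / 6.5² = 2.7% of the variance. The SE then falls by 1 − √(1 − 0.027) = 1.4%, before the small cost in step 5. Simulation of 4,000 null trials (four blocks, about 8.5 pre and 28 post women per block, residual SD 6.0, gravida worth 0.9 points per unit, previous stillbirth 3 points) gave mean SEs of 2.44, 2.40 and 2.36 with none, one and both. The second covariate saves 0.04/2.40 = 1.7%. Power for 3.5 points goes from about 31% to about 32%. Larger gains need stronger covariates: total R² of 0.05 gives SE 2.48 (power 29%), and R² of 0.30 gives SE 2.13 (power 38%).

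**5. Whether the sample can carry it.** Arm is a combination of the block indicators, so the model has 6 estimable parameters: 4 block levels, Time and the interaction. Residual degrees of freedom are 146 − 6 = 140 unadjusted, 139 with one covariate, 138 with two and 137 with three. Each covariate costs about 1/139 = 0.7% in variance.

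**6. The logistic models.** Expected events for EPDS ≥13 are 2 × 17 × 0.40 + 56 × 0.40 + 56 × 0.24 = 49.4. That is 8.2 per parameter with 6 parameters, 6.2 with two covariates added and 4.9 with four.

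**The case against.** The strongest defence is that one prespecified covariate is a reasonable parsimony rule in a small study, and that the benefit of a second is slight. On precision this is correct: the gain is under 2% of the SE on assumed inputs. Parsimony is also well founded for the logistic models. It is a weak argument for a linear model with about 140 residual degrees of freedom.

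The article does not demonstrate a differential shift. Independent research staff obtain consent and collect the data (Section 2.15), which narrows the route described above. The reachability criterion still runs through the ASHA. Section 3.1 acknowledges unmeasured time-varying confounding at block level and promises to report differences between enrolled and non-enrolled women. Neither step adjusts for measured characteristics of the women analysed.

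Three stronger readings are tempting and are not supported:

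- A reader might infer that the unnamed covariate permits selection after outcomes are seen and so inflates type I error. The text says that the choice is made a priori. Naming the variable is ordinary content for an analysis plan, and inflation would require breaking that commitment.
- A reader might count chance imbalance as bias. For the 15% factor, the difference-in-differences in prevalence has SD √(0.15 × 0.85 × (2/17 + 2/56)) = 14 points, or 0.42 EPDS points at 3 points each. That is already in the SE and is 0.42²/2.545² = 2.7% of the variance of β3. Previous stillbirth may also be the covariate that the plan includes.
- A reader might suppose that several prognostic variables are known to be collected. The article names two candidates and an unlisted set of sociodemographic characteristics.

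**Conclusion.** The cap is a stated rule that fits this design poorly. In a non-randomised repeated cross-section without a baseline score, the model leaves arm-differential changes in measured case mix in β3 and permits correction on only one variable. The sample does not require that limit for linear models.

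The consequence is moderate and conditional: 0.2–0.8 EPDS points if a shift of 10–20 points occurs in a factor worth 2–4 points. Those inputs are assumptions, and no such shift is shown. The case rests on protection against a plausible bias at almost no cost, with precision a minor benefit. Adjustment leaves the larger problem untouched: the interaction has about 28–35% power unadjusted, and about 38% even at R² of 0.30 with 17 pre-period women per arm.

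**What to change.** In Section 2.13, remove the one-covariate limit for the linear EPDS, SDS and BGQ models and prespecify gravida and previous stillbirth together. Both are settled by the time of the loss, so the intervention cannot affect them. Add a baseline sociodemographic variable only if it is confirmed as collected in all four blocks and is named before outcome data are seen. Report the unadjusted model alongside.

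State separately that the logistic models (EPDS ≥13 and BGQ ≥4) stay sparse because events are few. The article gives no expected event rate for BGQ ≥4.

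The cost is one sentence and one or two of about 140 residual degrees of freedom, at roughly 0.7% of variance each.

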#### Sensitivity analysis population

2.5.1

A pre-specified sensitivity analysis will additionally include women experiencing early neonatal death within 24 h of live birth in the study blocks during the same period.

The physiology of postpartum recovery is identical to that following stillbirth, and existing evidence demonstrates overlapping grief and depressive symptom profiles during the first six postpartum weeks (25, 26). However, as C-COMPASS was co-designed around the stillbirth experience-where the mother has not held a living infant-the counselling narrative requires sensitivity adaptation for women who briefly held a live-born baby.

Accordingly, early neonatal deaths will be enrolled separately with a subgroup identifier, excluded from the primary analysis, and included only in the pre-specified sensitivity analysis.

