### Sample size

2.12

Enrolment estimates are derived from SHRiSTI ASHA pregnancy surveillance data which indicates a mean of 4.6 stillbirths per block per month (range: 3.4–5.6), with a seasonal peak during July–October (5.2–5.6 per block per month) *(surveyed data from SHRiSTI project)*. This pattern is consistent with published systematic review by Lakhoo et al. on heat-associated stillbirth risk in South Asian settings in 2025. As described in Section 2.1, the SHRiSTI community-based surveillance estimate of 17.2 per 1,000 total births is used for planning, as it more accurately captures the true community-level burden than the HMIS facility-based figure.. The per-block estimate from the same surveillance data is 4.6 per month and this was used as a base for sample size. The study will employ a difference-in-differences (DiD) design across four blocks (two intervention, two control). With two blocks per arm, the expected enrolment rate is approximately 9.2 women per arm per month. Over the 8-week pre-intervention period, approximately 17 women per arm are expected, and over the 26-week post-intervention period, approximately 56 women per arm are expected, yielding a total sample of approximately 146 women.

The primary outcome is mean EPDS score (continuous). Assuming a clinically meaningful difference of 3.5 points, a pooled standard deviation of 6.5, two-sided alpha of 0.05, and 80% power, a minimum of 55 women per arm in the post-intervention period is required. The expected sample size of 56 per arm provides approximately 81% power. To account for an anticipated 10% attrition rate, the post-intervention data collection period may be extended to ensure a minimum effective sample size of 56 women per arm.

A pre-specified sensitivity analysis including early neonatal deaths (<24 h) is expected to add approximately 18 cases per arm. This estimate is based on a neonatal mortality rate of ∼22 per 1,000 live births in Haryana, with approximately 25% of deaths occurring within 24 h, applied to an estimated 277 live births per block per month. This yields approximately 1.5 early neonatal deaths per block per month, resulting in ∼18 additional cases per arm over the study period. The resulting post-intervention sample of approximately 74 per arm would provide approximately 91% power.

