
### Policy implications and future research

3.2

This study is designed from the outset to generate evidence that is actionable within India's government health system. The outcome measures, mean EPDS score, 72 h visit coverage rate, three-visit completion, referral completion, align directly with NHM programme monitoring indicators. The documentation pathway, a C-COMPASS column in the existing ASHA register, requires no new technology and no new reporting layer. The Tele-MANAS referral is already national infrastructure. If C-COMPASS achieves feasibility (≥70% 72 h coverage) and demonstrates a clinically meaningful reduction in mean EPDS score, the findings will be presented to the Haryana State Health Mission with a costed phased scale-up plan covering all six Palwal blocks, and subsequently to the national NHM technical advisory group for maternal mental health. The incremental cost analysis will provide the economic argument: if C-COMPASS can be delivered at a per-woman cost comparable to other NHM community interventions, the case for national integration becomes substantially stronger. The pre-specified sensitivity analysis for early neonatal deaths addresses the policy question of whether a single protocol can serve the full perinatal mortality framework population, if the answer is yes, the scope of the programme and its potential impact more than doubles without requiring protocol redesign. Future research priorities include a fully powered cluster-randomised controlled trial with the administrative block as the unit of allocation and a pre-specified intra-cluster correlation coefficient; longitudinal follow-up at 6 and 12 months to assess persistence of effects on grief and functional recovery; a formal health economic evaluation incorporating DALY metrics and multi-year programme costs; and deliberate protocol adaptation studies for early neonatal death, late miscarriage, and preterm birth with subsequent infant death, each requiring their own co-design process and piloting before evaluation. Also, systematic reviews and meta-analysis to generate evidence on effective interventions for promoting mental health in the reproductive continuum must be undertaken (28). The implementation science approaches applied in C-COMPASS, including quasi-experimental design for programme evaluation, mixed-methods feasibility assessment, and health systems integration, build on methodological frameworks previously applied to community-based child health programme implementation in comparable North Indian settings, where structured implementation research has demonstrated the value of embedding evaluations within existing health system infrastructure to generate actionable evidence for national programme scale-up (29, 30, 31).

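### In the early-neonatal-death sensitivity model the Arm × Time coefficient, under the usual coding, still targets the stillbirth effect, and the stated 91% power belongs to a pooled post-period comparison, not to any contrast in that model

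*Protocol article*

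**What the plan says.** Section 2.13 gives the primary model as a linear regression with Arm, Time, Arm × Time and block effects, and states that the Arm × Time term "represents the DiD estimator" (β₃). The sensitivity analysis refits this model in the expanded population, "incorporating a perinatal loss type indicator and its interaction with the intervention effect". The article does not give the coding of loss type, the lower-order loss-type terms, or the coefficient or contrast to be reported.

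Under section 2.5.1, women with an early neonatal death are "excluded from the primary analysis, and included only in the pre-specified sensitivity analysis". The matching secondary objective in section 2.3.1.2 is to explore whether the effects stay consistent once these women are included.

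Section 2.12 plans as follows: "Assuming a clinically meaningful difference of 3.5 points, a pooled standard deviation of 6.5, two-sided alpha of 0.05, and 80% power", so that "a minimum of 55 women per arm in the post-intervention period is required". For the expanded population it says: "The resulting post-intervention sample of approximately 74 per arm would provide approximately 91% power". Section 3.2 says that this analysis "addresses the policy question of whether a single protocol can serve the full perinatal mortality framework population", and that a positive answer would more than double the scope of the programme.

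**The concern.** Two statements about the same analysis do not fit together. Section 2.13 splits the intervention effect by loss type. Section 2.12 gives the power of a single effect pooled over loss types, and computes it without the pre-intervention period.

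Once loss type interacts with the intervention effect, β₃ is the effect in the reference group. If that group is stillbirth, the coefficient that the protocol calls its estimator has the same target in the sensitivity analysis as in the primary one. Agreement between the two would then be expected whatever happens among women with a neonatal death. The information on consistency sits in the interaction term, which is imprecise.

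At stake is the policy reading in section 3.2. A stable β₃ or a non-significant interaction, set beside a stated 91% power, could be taken as support for one protocol for both groups. Section 2.5.1 itself says that the counselling narrative needs adapting for women who briefly held a live-born baby, so a different effect in that group is plausible.

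**Working it through.** **Inputs.** From section 2.12: difference 3.5, SD 6.5, two-sided α 0.05; per arm 17 stillbirths pre-intervention and 56 post-intervention; 18 added neonatal deaths per arm; 1.5 neonatal deaths per block per month. The 18 equals 1.5 × 2 blocks × 6 months, and 56 + 18 = 74, so all 18 are counted in the post-intervention period.

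Assumptions: loss type coded 0 = stillbirth, 1 = neonatal death; about 6 neonatal deaths per arm pre-intervention (1.5 × 2 × about 1.85 months for 8 weeks = 5.5); two equal blocks per arm; independent errors; no attrition.

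**The plan's own figures.** Power = Φ(3.5/SE − 1.96), with SE = 6.5 × √(2/n).
- n = 56: SE 1.228, power 81.3%. The stated 81% reproduces.
- n = 74: SE 1.069, power 90.6%. The stated 91% reproduces.

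Both are post-period two-sample comparisons with no pre-period term.

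**What β₃ targets.** Stillbirth effect fixed at −3.5:

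| Neonatal-death effect | β₃, interaction model | Interaction term | β₃, loss type as main effect only |
|---|---|---|---|
| −3.5 | −3.50 | 0.00 | −3.50 |
| 0 | −3.50 | +3.50 | −2.65 |
| +3.5 | −3.50 | +7.00 | −1.80 |

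The pooled value can be recovered from the interaction model as β₃ + (18/74) × interaction: −3.50 + 0.243 × 3.50 = −2.65, and −3.50 + 0.243 × 7.00 = −1.80.

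**How close β₃ is to the stillbirth-only fit.** The stillbirth-only DiD has SE 6.5 × √(2/17 + 2/56) = 2.55.
- Loss type and the three-way term only: β₃ has SE 2.26 and correlation 0.89 with the stillbirth-only estimate. The target is the same but the number is not, because the added women help to estimate the shared block and time effects.
- Loss type × Arm and loss type × Time also included: SE 2.55, correlation 0.9999.

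**Precision of the interaction.**
- Three-way term without the lower-order products (from the design matrix): SE 2.23, 95% CI ± 4.4, power 35% for a 3.5-point difference between loss types.
- All lower-order terms: SE 6.5 × √(2/17 + 2/56 + 2/6 + 2/18) = 5.03, 95% CI ± 9.9, power 10%.
- On section 2.12's post-period basis: SE 6.5 × √(2/56 + 2/18) = 2.49, power 29%; 80% power needs a difference of about 7.0 points.

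**Precision of the pooled DiD effect.** SE = 6.5 × √(2/23 + 2/74) = 2.19, where 23 = 17 + 6. Power = Φ(3.5/2.19 − 1.96) = 36%.

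**Range.** With 5 rather than 6 neonatal deaths pre-intervention, the SE is 2.23 and power 35%. Section 2.4 gives a pre-intervention period of 10–12 weeks against the 8 weeks of section 2.12. At 12 weeks (about 25 stillbirths and 8 neonatal deaths per arm), the SE is 6.5 × √(2/33 + 2/74) = 1.92 and power 44%; the full interaction SE is 4.49.

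**Where the gap comes from.** The fall from 91% to 36% is due to the pre-period term 2/23, not to the interaction. The same term takes the primary figure from 81% to Φ(3.5/2.55 − 1.96) = 28%.

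**The case against.** The strongest reply is that the model was given an interaction precisely to answer the consistency question. If the effects differ by loss type, the interaction shows it: its expectation is +3.5 or +7.0 in the scenarios above. A weighted contrast, or a centred loss-type indicator, returns the pooled effect with almost no loss of precision (SE 2.20 against 2.19). This stands. A reader might infer that the sensitivity analysis cannot disagree with the primary one, or that the added women contribute nothing to β₃. The documents do not support either reading. The first ignores the interaction term. The second holds only if all lower-order loss-type terms are fitted.

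It can also be said that coding, lower-order terms and the reported contrast are usual content for an analysis plan that is not shown. That is fair, and the text does not say that the lower-order terms are left out; their absence is not charged here.

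Finally, the objective is worded as exploratory, section 3.2 is conditional and itself calls for separate adaptation studies for early neonatal death, and nothing says that a non-significant interaction would count as proof. This limits the harm. It does not make the stated 91% the power of any contrast in the specified model.

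**Conclusion.** The point holds in a limited form. Under stillbirth-reference 0/1 coding, β₃ in the sensitivity model targets the stillbirth effect and, read alone, does not answer the consistency objective. The interaction does address it, with an SE of about 2.2 to 5.0 EPDS points depending on the lower-order terms. The model can therefore answer the question, but weakly, and the article does not say which number is the answer.

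The firmer part is the power statement. The 91% is arithmetically correct for a pooled post-period comparison of 74 per arm, but section 2.13 specifies neither a pooled effect nor a post-period comparison. The pooled DiD effect has about 36% power (35% to 44% over the pre-period assumptions tried). That shortfall is not specific to this analysis: it comes from sizing on the post-intervention comparison and applies equally to the primary 81%.

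The size of the problem rests on the assumed coding, on about 6 pre-intervention neonatal deaths per arm and on independent errors. The primary estimate is unaffected by how the sensitivity model is specified.

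**What to change.** In section 2.13:
- Name the pooled DiD effect in the expanded population as the sensitivity estimate, from a model with loss type as a main effect only or from the equivalent weighted contrast. Report it beside the stillbirth-only β₃.
- Report the loss-type interaction and the neonatal-death-specific effect separately, as exploratory, with 95% confidence intervals, from a model that includes loss type × Arm and loss type × Time. State the coding.
- State that a non-significant interaction is not evidence that one protocol serves both groups.

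In section 2.12, replace the 91% with the power of the DiD contrast (about 36% on the stated counts and the assumption above), or delete it.

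The cost is a few sentences and one further model run. No change to recruitment or data collection is needed.
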